## Abstract

**Background:**

Tumor cells killed by radiation therapy (RT) are a potentially good source of antigens for dendritic cell (DC) uptake and presentation to T-cells. RT upregulates cell death receptors such as Fas/CD95 and MHC-I, induces the expression of co-stimulatory molecules on tumor cells, and promotes production of pro-inflammatory cytokines. High-dose interleukin-2 (HD-IL-2) bolus has been shown to obtain objective response rates ranging from 15% to 17% in patients with metastatic melanoma or renal cell carcinoma (RCC), with 6% to 8% of cases experiencing a durable complete response. However, HD-IL-2 is also associated with severe side-effects; if it is to remain a component of the curative treatment strategy in patients with metastatic melanoma or RCC, its therapeutic efficacy must be improved and patients who are most likely to benefit from treatment must be identified *a priori.* We designed a clinical study combining immunomodulating RT and HD-IL-2 to evaluate their clinical and immunological efficacy and to explore the predictive and prognostic value of 1) tumor-specific immune response and 2) serum levels of proangiogenic cytokines.

**Methods/design:**

The primary endpoint of this proof-of-principle phase II study is immune response. Secondary endpoints are the identification of biomarkers potentially predictive of response, toxicity, response rate and overall survival. Three daily doses of booster radiotherapy (XRT) at 6–12 Gy will be administered to at least one metastatic field on days −3 to −1 before the first and third cycle. Treatment with IL-2 (dose 18 MIU/m2/day by continuous IV infusion for 72 hours) will start on day +1 and will be repeated every 3 weeks for up to 4 cycles and then every 4 weeks for a further 2 cycles. Immune response against tumor antigens expressed by melanoma and/or RCC will be evaluated during treatment. Circulating immune effectors and regulators, *e.g.* cytotoxic T lymphocytes and regulatory T cells, as well as serum levels of proangiogenic/proinflammatory cytokines will also be quantified.

**Discussion:**

This study aims to evaluate the potential immunological synergism between HD-IL-2 and XRT, and to identify biomarkers that are predictive of response to IL-2 in order to spare potentially non responding patients from toxicity.

**Trial registration:**

EudraCT no. 2012-001786-32

ClinicalTrials.gov Identifier: NCT01884961

## Background

The concept that the immune system can distinguish the neoplastic from the normal self was proposed almost a century ago. Both cellular and humoral antitumor immune responses to tumor-associated antigens (TAAs) have been observed in many cancer patients. Tumors are genetically unstable, and the emergence of new genetic variants ensures that tumors survive in spite of the host’s immune system. Tumor development involves a prolonged series of checks and balances between the host, attempting to curtail tumor growth, and the tumor, benefitting from genetic changes, altering the microenvironment and avoiding immune elimination. Within this context, the “immunoediting hypothesis” suggests that the host’s immune system is capable of edit for the survival of tumors that become resistant to immune cells by eliminating cancer cells sensitive to immune attack [1-5].

Ionizing radiation therapy (RT) is known to kill cancer cells and other cells within the tumor stroma, including endothelial cells and intratumoral lymphocytes. The cell surface translocation of calreticulin or the extracellular release of high-mobility group protein B1 (HMGB1,a nonhistone nuclear protein), are among the molecular signals required to have an “immunogenic cell death”. Ionizing radiation may induce these changes and promote immunogenic cell death, favoring the development of an effective immune response [6-8]. Tumor cells killed by RT should, in theory, be a very good source of antigens for dendritic cell (DC) uptake and presentation of T cells [9,10]. The optimal activation of T cells by DC can only be achieved in the presence of inflammatory or “danger” signals. Although these danger signals can be generated by radiation exposure, their nature remains largely undefined [11]. Proinflammatory cytokines IL-1β and TNF-α can also be induced by radiation [12,13]. In addition, RT can upregulate cell death receptors such as Fas/CD95 and MHC-I and costimulate specific tumor cells, enhancing their tendency to either die or be recognized [14,15]. Finally, RT has complex effects on the tumor microenvironment: in particular, radiation-induced inflammatory signals, changes in extracellular matrix proteins, and the expression of adhesion molecules by endothelial cells of tumor vessels all facilitate the homing of both antigen-presenting and effector T cells to the tumor [16-18].

Demaria et al. recently showed in a murine model that irradiation of a grafted tumor generated an immune response against tumor cells and that this immune response inhibited the growth of tumor grafted outside the irradiation field. This anti-tumor effect was hypothesized to be the result of a specific immune response as it was not observed in immunodeficient mice (T-cell deficient, nude mice), was tumor-type specific (growth of a second graft of a different cell line was not affected by irradiation of the first graft), and synergized with administration of the FMS-like tyrosine kinase 3 (Flt-3) ligand. Indeed, the use of Flt-3 alone had no influence on the second graft, suggesting that the effect was not due to an unspecific boost of immunity induced by the Flt-3 ligand, but rather to the amplification of a tumor-specific response induced by the tumor irradiation. These data indicate that radiotherapy can prime the immune system against similar cells some distance away from the irradiation field (abscopal effect) and that, in the absence of an additional immune system stimulation, the radiation-induced immune response has no clinical effect [19-21]. However, optimal radiation regimens have yet to be defined. Formenti et al. compared different radiation regimens in combination with anti-CTLA-4 and found that a hypofractionated regimen (8 Gyx3) was more effective than a single dose of 20 Gy [8].

High-dose interleukin-2 (HD-IL-2) has been reported to induce an objective clinical disease regression in 15 to 17% of patients with metastatic melanoma and renal cell carcinoma, with 6% to 8% of cases experiencing a durable complete response of all metastases [22-24]. The first role attributed to IL-2 was its potent capacity to enhance in vitro T-cell proliferation and differentiation, and for this reason it was originally named T-cell growth factor. Following these initial descriptions of IL-2 function, a number of studies highlighted numerous contradictory functions of the cytokine. There is also evidence that IL-2 is an important factor in the generation of memory T-cells which undergo secondary expansion when they re-encounter an antigen. However, in contrast to these immune-enhancing functions, IL-2 also promotes activation-induced cell death (AICD) of T-cells and has anti-inflammatory properties [25].

Analogously to IFN-gamma, IL-2 limits IL-17 production and exerts its immunosuppressive function by stimulating the generation and homeostasis of regulatory T cells (Tregs) [26]. In fact, IL-2 is known to be a non-redundant factor in the in vivo homeostasis of Tregs which constitute a fundamental part of immunological self-tolerance and immune regulation [25]. IL-2 eradication of tumors is thought to be mediated by enhanced T-cell function and increased T-cell numbers. Lymphopoiesis is partially driven by lymphopenia and homeostatic proliferation. During homeostatic recovery, even in the absence of antigen stimulus, lymphocyte subpopulations shift, favoring antigen-experienced memory phenotypes and enhanced effector cell function. However, although the antitumor effect of HD-IL-2 is not completely understood, it appears to induce the release of proinflammatory cytokines into the blood and at the tumor site, enabling the ingress of inflammatory cells and promoting the cytolytic- and cytokine-producing activity of recruited lymphoid cells. This process drives the activation of monocytes/macrophages and other tumor-infiltrating immune cells, recruits immune cells from the periphery and triggers so-called *epitope spreading*, with novel determinants recognized in the context of the emergent immune response. HD-IL-2 suppresses CD4 + CD25hi-FoxP3+ T-regulatory cells, the prime contact-dependent suppressors of antigen-specific T cell response in metastatic melanoma patients, with a demonstrable clinical benefit.

Clinical evidence for an immune-mediated HD-IL-2 mechanism of action is based on tumor regression, the development of organ-specific autoimmunity in responders such as delayed-onset vitiligo, observed in some of our patients, and the onset of autoimmune thyroiditis. Thyroiditis was the first autoimmune disease reported to be induced by HD-IL-2 and which correlated with a favorable clinical outcome. As interleukin-2 paradoxically affects both tolerance and immunity in the absence of T-regulatory cells, HD-IL-2 increases effector CD8+ cytotoxic function which is responsible for both autoimmunity and tumor regression. Cancer immunotherapy with IL-2 has the potential to cure a subset of patients who need to be identified before treatment in order to minimize toxicity and improve therapeutic index [25,27,28].

Prospective clinical trials have reported a response rate of around 16% for melanoma patients treated with IL-2. Data suggest that higher rather than lower dose regimens are more likely to induce tumor regression in both melanoma and RCC. A retrospective analysis of 270 patients with metastatic melanoma treated with HD-IL-2 between 1985 and 1993 reported objective response rates of 16%, including a complete response rate of 6%. The median response duration was 6.5 months, and 60% of complete responders were progression-free after 5 years [29]. A major difference between the HD bolus IL-2 regimen and other chemotherapeutic melanoma therapies lies in the duration and quality of the responses obtained. Of the 24 patients receiving HD-IL-2 regimens at the National Cancer Institute who experienced a complete response (CR), 19 remained in complete remission for 46 to 137 months. In the past, several studies have focused on IL-2/chemotherapy combinations in metastatic melanoma. Although randomized trials have not been conducted to date, the HD-IL-2 bolus (600,000 to 720,000 U/kg intravenous (IV) every 8 hours for 15 doses) administered in the original NCI studies would seem to be superior to continuous IV infusion IL-2 [30]. Although response rates are comparable, they tend to be of shorter duration. In 7 published studies on metastatic RCC, objective responses (OR), complete responses (CR) and partial responses (PR) were seen in 15, 7, and 8% of patients, respectively. Furthermore, the median duration of response was 54 months for all responders, 20 months for PRs, and was not reached for CRs. The median survival was 16 months for all 255 patients [31]. However, HD-IL-2 administration is associated with numerous side-effects may thus have an impact on every organ system in the body. In fact, there is substantial variation in the toxicities experienced by patients receiving high-dose IL-2 which are thought to result primarily from capillary leak syndrome (CLS) and lymphoid infiltration, the latter observed histologically in many organs [32,33]. Sondel *et al.* studied continuous IL-2 infusion for 4–7 days at a dose of approximately 9 MIU/m2/day [34]. In addition, Dillman *et al.* demonstrated the efficacy of a higher dose continuous infusion IL-2 regimen (18 MIU/m2/day) over 5 days during which CLS proved to be the limiting toxicity [35]. The same group studied a 96-hour continuous infusion regimen for melanoma patients, reporting that it was better tolerated, with no decrease in response rate [36]. Continuous infusion may be more beneficial than bolus dosing in terms of inducing a higher degree of LAK cytotoxicity and higher rebound lymphocytosis. For these reasons, Quan *et al.* used the 72-hour high-dose continuous infusion schedule more frequently, reporting good tolerance and activity in both melanoma and renal cell carcinoma [37]. In an attempt to reduce the severity of CLS, Rosenberg’s group used concomitant corticosteroid infusion during IL-2 therapy, observing that the cytotoxic function of CD8 + T lymphocytes was not affected and that side-effects were reduced [38]. It is clear that, if HD-IL-2 is to remain a component of a curative treatment strategy in patients with metastatic melanoma or RCC, its therapeutic index will have to be improved.

Two active areas of investigation within the field of immunotherapy focus on the elimination of immune suppression/regulation and the improvement of patient selection.

Based on an understanding of the mechanisms of action of IL-2, biomarkers of response to this cytokine might allow us to identify a subset of patients who could potentially benefit from treatment. To date, the majority of putative predictors of IL-2 response have been post-treatment variables, such as the height of rebound lymphocytosis, treatment-induced thrombocytopenia, the development of autoimmune thyroiditis and vitiligo, and the decrease in the absolute number and frequency of peripheral Tregs.

In renal cell carcinoma, the level of carbonic anhydrase IX (CAIX) in primary tumors has been found to be a potentially useful pretreatment predictor. In both melanoma and RCC, serum vascular endothelium growth factor (VEGF) and fibronectin have also been identified as independent predictors of non response, and high levels of these proteins have been correlated with a lack of clinical response and decreased overall survival. Other analyses of pretreatment factors have correlated IL-2 with the Cw7 phenotype or low serum levels of IL-6 and C-reactive protein, but none has proven to be sufficiently predictive of clinical benefit to be useful in patient selection for IL-2 therapy [39-44].

## Methods/design

### Objectives

This is a proof-of-principle phase II study to assess 1) immune response and 2) potential biomarkers predictive of response to treatment with HD-IL-2.

### Primary objective

The primary objective of this study is to determine the immunological efficacy of the combined RT/HD-IL-2 treatment (assessed by IFN-g ELISPOT analysis) in terms of its ability to enhance the proportion of a selected panel of circulating immune effectors specific for tumor antigens known to be expressed in RCC and/or melanoma.

### Secondary objectives

to prospectively determine the predictive value of pretreatment biomarkers in identifying patients who could potentially benefit from combined RT/HD-IL-2 treatment, *i.e.* serum levels of VEGF-A, fibronectin, proinflammatory cytokines (IL-1beta, IL-6, IL-8, IL-10, IL-12, alphaTNF), tumor tissue expression of CAIX for RCC and presence of N-Ras mutation for melanoma.ToxicityResponse rateOverall survival

### Trial design

#### Summary of trial design

Single center, open-label proof-of-principle phase II trial to assess immune response and predictive biomarkers of response.

Three daily doses of booster radiotherapy (XRT) at 6–12 Gy to 1–5 metastatic fields will be administered on days −4 -3 -2 or −3 -2 -1 before the first and the third cycle of IL-2. IL-2 will be administered on day +1 of each cycle.

Treatment with IL-2 (dose 18 MIU/m2/day in 500 cc by continuous IV infusion for 72 hours) will start on day +1 and will be administered every 3 weeks for up to 4 cycles, then every 3–4 weeks for a further 2 cycles.Total duration of the trial: 36 months:Enrollment period: 20 monthsTreatment: maximum of 6 cycles (5 months) per patientFollow-up every three monthsStep 1: 7 patients will be enrolled; on the basis of a minimax two-stage Simon design, a 40% immune response will preclude further study, whereas a 70% response rate will indicate that further study is warranted. Using alfa and beta errors of 0.10, if an immune response is observed in at least 3 of the 7 patients enrolled during the first stage, the study will go on with:Step 2: recruitment of a further 12 patients.

The treatments will be considered active if an immune response is observed in 11 out of 19 patients treated. The analysis will be performed on an intention-to-treat population, *i.e.* all patients receiving at least one cycle of therapy.

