### Dose delays/modifications

NCI Common Toxicity Criteria version 4.0 (available at: http://www.eortc.be/services/doc/ctc/CTCAE_4.03_2010-06-14_QuickReference_5x7.pdf) will be used. No dose reductions of IL-2 are allowed. Dose delays within the same cycle: IL-2 doses will be delayed on the basis of the symptomatic recovery from the previous dose. A delay longer than 24 hours will result in discontinuation of that cycle of IL-2.

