
### Statistical considerations

#### Study design/endpoints

Single center, open-label proof-of-principle phase II trial to assess immune response and biomarkers potentially predictive of response. The primary objective of this study will be ***immunological efficacy***, as assessed by quantification of circulating immune effectors specific for a selected panel of tumor antigens. Secondary endpoints will be the predictive value of pretreatment serum biomarkers in identifying patients who are likely to benefit from high-dose IL-2-based therapy, toxicity, response rate (RR) and overall survival (OS). The analysis will be performed on an intention-to-treat population, *i.e.* all patients who have received at least one cycle of therapy. All time-dependent clinical endpoints (RR and OS) will be estimated with the Kaplan-Meier method. Frequency tables will be performed for all categorical variables. Continuous variables will be presented using mean and standard deviation or median and range.

Given the explorative intent of the study and the limited sample size, we are aware of being exposed to a high level of false-positive results. Unless otherwise indicated, analysis of demography and baseline characteristics will be performed on all enrolled patients. Demographic and laboratory results will be summarized using descriptive statistics. The percentage of patients reporting an adverse event (AE) up to 30 days after the end of HD-IL-2 treatment will be calculated with 95% confidence intervals by type of AE. The overall rate of grade 3–4 related AEs will be calculated. In addition, summary statistics of clinically significant laboratory abnormalities will be tabulated. The time of disease progression and the initiation of new therapies will also be documented.

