### Sample size/accrual rate

This is a proof-of-principle trial with a minimax two-stage design:Step 1: 7 patients enrolled. A 40% immune response will preclude further study, whereas a 70% response rate will indicate that further study is warranted. Using alfa and beta errors of 0.10, if an immune response is observed in at least 3 of the 7 patients enrolled during the first stage, the study will go on with:Step 2: recruitment of 12 additional patients.

Treatments will be considered active if an immune response is observed in 11 out of 19 patients treated. An enrolment period of 20 months is planned, with an accrual rate of about 1 patient per month. There are no patient stratification factors planned.

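### The set labelled intention-to-treat requires a received cycle, so some treated patients leave the response denominator and, by default, the toxicity rates

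*Protocol article*

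**What the plan says.** **Analysis set.** The protocol article defines it twice. Under Summary of trial design, directly after the final decision rule, the intention-to-treat population is "all patients receiving at least one cycle of therapy". Under Statistical considerations (Study design/endpoints), directly after the list of secondary endpoints, it is "all patients who have received at least one cycle of therapy". Only demography and baseline characteristics are placed on all enrolled patients. No separate safety population is named.

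**Decision rule.** The section Sample size/accrual rate continues the trial if a response is seen in "at least 3 of the 7 patients enrolled during the first stage". It then states: "Treatments will be considered active if an immune response is observed in 11 out of 19 patients treated". The first rule counts enrolled patients and the second counts treated patients.

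**Course of treatment.** Three radiotherapy fractions are given before the first IL-2 cycle (Radiotherapy), and each IL-2 cycle is a 72-hour infusion (High-dose IL-2). A started cycle can be cut short: "A delay longer than 24 hours will result in discontinuation of that cycle of IL-2" (Dose delays/modifications).

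**Toxicity summary.** Adverse events are to be given as percentages by type with 95% confidence intervals. The one overall severity figure is described thus: "The overall rate of grade 3–4 related AEs will be calculated".

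**The concern.** An intention-to-treat set should not depend on what happens after treatment starts. This one does, and a cycle that is stopped for intolerance is stopped because of an outcome the trial measures.

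Two kinds of patient are affected:

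- those irradiated who never receive IL-2, who are excluded however the definition is read;
- those whose first IL-2 cycle is discontinued, who may be excluded, since *received* is not defined for a partial cycle.

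The decision rule adds to the uncertainty, because enrolled, treated and at-least-one-cycle patients are three different denominators. With 7 and 19 patients, the status of one or two matters. At stake are the reported immune response proportion, the reported toxicity and, if excluded patients are replaced, the type I error of the decision.

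A related gap is that a rate limited to grades 3 and 4 leaves out a fatal related event.

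**Working it through.** **Inputs from the protocol article.** Null and target response rates are 0.40 and 0.70 ("a 40% immune response will preclude further study, whereas a 70% response rate will indicate that further study is warranted"). Error rates: "Using alfa and beta errors of 0.10". Stage 1 has 7 patients, continuing if at least 3 respond. Stage 2 adds 12, and activity is declared if at least 11 of 19 respond.

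**Assumption.** The share *d* of patients who start treatment but fall outside the set is not given. I use 5% to 20% as a range and take these patients to be non-responders.

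**1. The plan's own figure.** With response probability *p*,

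P(active | p) = Σ over x = 3 to 7 of P(X₁ = x; 7, p) × P(X₂ ≥ 11 − x; 12, p).

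This gives P(active | 0.40) = 0.0841 and P(active | 0.70) = 0.9028. Both meet the stated error rates, and a search of two-stage designs returns this one as the minimax design. The sample size is not in error.

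**2. Excluded, not replaced, absolute cut-offs kept.** A non-responder adds nothing to either count, so the comparisons with 3 and 11 are unaffected and the type I error stays at 0.084. Only the reported proportion moves. As an illustration with assumed counts, take 10 responders among 19 who start and 2 excluded non-responders. The report would give 10/17 = 58.8% instead of 10/19 = 52.6%. The count of 10 fails the rule either way, although 58.8% lies above 11/19 = 57.9%.

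**3. Excluded and replaced until 19 qualify.** If the true rate among all who start is 0.40, the rate among those counted is 0.40/(1 − d). Putting this into the formula of step 1:

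| d | Rate among counted | P(active) |
|---|---|---|
| 0% | 0.400 | 0.084 |
| 3% | 0.412 | 0.103 |
| 5% | 0.421 | 0.117 |
| 10% | 0.444 | 0.163 |
| 15% | 0.471 | 0.226 |
| 20% | 0.500 | 0.311 |

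The planned 0.10 is passed at a loss of about 3%.

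**4. Toxicity, assumed counts.** Suppose 2 of 19 stop in cycle 1 with a grade 3–4 event and are excluded, and 6 of the other 17 have such an event. The reported rate is 6/17 = 35% instead of (6 + 2)/19 = 8/19 = 42%. Here the exclusion changes both the numerator and the denominator.

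**5. Power when losses count as non-responders.** If 70% applies only to patients who receive a cycle, the rate among all who start is 0.70 × (1 − d):

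| d | Rate among all who start | Power |
|---|---|---|
| 0% | 0.700 | 0.903 |
| 5% | 0.665 | 0.834 |
| 10% | 0.630 | 0.742 |
| 20% | 0.560 | 0.512 |

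**The case against.** **Type I error.** A reader might infer that the stated error rate of 0.10 fails. The article does not support that as it stands. It fixes 7 patients plus 12 more with absolute cut-offs and says nothing about replacement. Read literally, the decision and the 0.084 are unchanged. This stands, and the figures in step 3 are conditional. Replacement is not ruled out either, and a rule calling for 19 treated patients leaves room for it.

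**Responder count.** It is also tempting to say that early failures leave the responder count. If they are non-responders they were never in it; they leave only the denominator.

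**Interrupted first cycles.** Exclusion of these patients is an ambiguity, not a stated rule. The section Study treatment modifications foresees stopping for intolerance as part of giving a cycle, so such a cycle could be taken as received. The group excluded for certain, irradiated but never given IL-2, arises only in the few days between radiotherapy and day +1 and may be very small.

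**Who is lost.** One might suppose that the lost patients are mainly toxicity or early-progression failures. The documents give no such breakdown. Entry requires a life expectancy above 3 months and the first restaging is at 8 weeks, so documented progression within cycle 1 would be unusual. The values of *d* have no anchor in the text.

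**Toxicity.** The adverse-event sentences name no population, so the restricted set applies only by default, and a full protocol or analysis plan may name a safety set. Fatal events are not lost to the trial: adverse events are tabulated by type without a grade limit, and the Death on study paragraph requires all deaths to be recorded. Only the one overall rate omits them.

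**Exploratory purpose.** The article openly accepts a high risk of false-positive results. That lowers the stakes but does not settle which patients are counted.

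**Conclusion.** The point holds as a correction that should be made, not as a flaw that invalidates the design. The two-stage design reproduces exactly. What is wrong is the stated set: its label contradicts its definition, it excludes some patients who have received study treatment, it leaves partial first cycles undecided, and it does not match the enrolled and treated denominators of the decision rule.

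The size depends on practice the article does not fix. Without replacement, and with 3 and 11 kept as counts, the decision does not change; the response proportion is overstated and toxicity may be understated. With replacement of non-responders, the chance of a false declaration of activity is 0.117 to 0.311 for assumed losses of 5% to 20%, against 0.084 with no loss.

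**What to change.** - Define the primary and safety set as every enrolled patient who starts any study treatment: a first radiotherapy fraction or any IL-2.
- State that patients are not replaced.
- Apply both 3 of 7 and 11 of 19 to that set, counting patients without an assessable post-treatment ELISPOT as non-responders, and use one term for the denominator throughout.
- Keep the at-least-one-cycle set as a labelled sensitivity analysis without the intention-to-treat label, and say whether a partial cycle qualifies.
- Report toxicity on the same set, and give the overall rate of related adverse events as grade 3 or higher.

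**Cost.** No new data are needed. The reported response rate may be lower and the toxicity rate higher. If the 70% target was meant only for patients who receive a cycle, power is 0.834 at 5% loss and 0.742 at 10%, not 0.903, so the sponsor should confirm which patients the target describes. This cost is relative to a trial in which all 19 receive a cycle. Under the present fixed numbers and counts, read without replacement, the same loss of power is already there.
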